### Sample size

In each country, trained study staff will weigh up to 1,064 infants to identify and randomize 72 with birth weight ≤2500g and 90 who weigh <2600g on day 4. With respect to the primary aim, determining the impact of formula on WAZ at 30 days of infant age, the anticipated sample size of 324 dyads (144 LBW infants and 180 infants with low weight on day 4 under equal randomization) will provide 80% or greater power per weight stratum for intervention group comparison to detect a difference of 0.20 with respect to the outcome of WAZ at day 30 for the entire study cohort after accounting for up to 20% loss to follow-up. This sample size will also allow the estimation of the mean difference between WAZ at day 30 and WAZ at birth with 0.17 and 0.15 standard errors by intervention group, respectively, for the entire study cohort. Including both mothers and infants, the total sample size for the randomized trial is anticipated to be 324 mothers and 324 infants, or 648 individual participants in total.

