## Abstract

Childhood undernutrition is a major health burden worldwide that increases childhood morbidity and mortality and causes impairment in infant growth and developmental delays that can persist into adulthood. The first weeks and months after birth are critical to the establishment of healthy growth and development during childhood. The World Health Organization recommends immediate and exclusive breastfeeding (EBF). In infants for whom EBF may not meet nutritional and caloric demands, early, daily, small-volume formula supplementation along with breastfeeding may more effectively avoid underweight wasting and stunting in early infancy than breastfeeding alone. The primary objective of this randomized controlled trial is to evaluate the efficacy of formula for 30 days among low birth weight (LBW) infants <6 hours of age and those not LBW with weights <2600 grams at 4 days of age. We will compare breastfeeding and formula (up to 59 milliliters administered daily) through 30 days of infant age vs recommendations for frequent EBF without supplementation, and test the hypothesis that formula increases weight-for-age z-score at 30 days of infant age. The trial will enroll and randomize 324 mother-infant pairs in Guinea-Bissau and Uganda, and follow them for 6 months for outcomes including growth, intestinal microbiota, breastfeeding duration, infant dietary intake, and adverse events. Conservatively estimating 20% loss to follow up, this sample size provides ≥80% power per weight stratum for intervention group comparison to detect a difference of 0.20 with respect to the outcome of WAZ at day 30. This trial was approved by the University of California, San Francisco Institutional Review Board (19–29405); the Guinea-Bissau National Committee on Ethics in Health (Comite Nacional de Etica na Saude, 075/CNES/INASA/2020); the Higher Degrees, Research and Ethics Committee of Makerere University (871); and the Uganda National Council of Science and Technology (HS1226ES). We plan to disseminate study results in peer-reviewed journals and international conferences.

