### Outcomes

The primary study outcome is infant WAZ at 30 days of infant age. We hypothesize that feeding formula to infants will increase infant WAZ at 30 days of infant age by 0.20 compared to infants randomly assigned to recommendations for EBF without supplementation. Secondary, exploratory, and safety study outcomes include infant WLZ at 30 days of infant age; WAZ, WLZ, and LAZ through 6 months of age; breastfeeding duration; abundance of *B*. *infantis* in the intestinal microbiota at 30 days of age; adverse events; and serious adverse events. We hypothesize that feeding formula will increase infant WLZ at 30 days of infant age and infant WAZ, WLZ, and LAZ through 6 months of age by 0.20 compared to infants randomly assigned to recommendations for EBF without supplementation. While we hypothesize that infant breastfeeding duration will not differ between these feeding interventions, we hypothesize that the abundance of *B*. *infantis* in the intestinal microbiota will be higher among infants at 30 days of age who receive formula than among those who do not. To ensure infant safety, the effect of formula on mortality will be assessed after every 20 randomized infants have completed 30 days of follow-up, and the effect of formula on mortality and SAEs will be assessed once 25% and once 50% of randomized participants have completed 30 days of follow-up.

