### Statistical analyses

Our primary analysis will be intention-to-treat which will inform the primary global health policy question of whether recommending formula improves infant growth. In order to account for our planned stratified randomization, we will use a permutation test, permuting the infant feeding intervention assignment within the infant weight stratum, to determine the effect of formula on the primary outcome of WAZ at 30 days of infant age as well as on the secondary and exploratory outcomes of WLZ at 30 days, WAZ, WLZ and LAZ through 6 months, intestinal microbiota at 30 days of age, breastfeeding duration, and receipt of non-breast milk dietary intake between birth and 6 months of age.

To determine *B*. *infantis* abundance, stool samples will be shipped to University of California, Davis for analysis and assessed by 16S rRNA gene sequencing. Samples found to have sequences from the *Bifidobacteriaceae* family will be further subjected to analysis of bifidobacterial species-specific terminal restriction fragment length polymorphisms (Bif-TRFLP) to identify specific species of *Bifidobacterium*. Statistical differences in *B*. *infantis* abundance between supplemented and unsupplemented infants, while accounting for strata, will be assessed by mixed linear modeling. In additional exploratory analyses, we will use cluster and eigenstructure analyses (e.g., principal component analysis) for descriptive analysis of 16S rRNA gene abundance data, followed by adonis permutation tests for significance of associations with continuous or factor variables or Mantel tests for associations between distance matrices. For example, feeding intervention group is an important factor variable; a significant association of the 16S rRNA gene profile with group membership would suggest an effect of formula on microbiota. Additional exploratory analyses will be undertaken with supervised machine-learning approaches, in order to identify new and unexpected features unique to the intestinal environment of formula recipients. For example, random forests will be used to identify important features separating the microbiotas of formula from EBF recipients.

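### The claimed 80% power in each weight stratum for a 0.20 WAZ difference conflicts with the plan's own standard errors, which imply about 19–26% per stratum and 36–43% pooled

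*Protocol article*

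**What the plan says.** The Sample size section plans for "324 dyads (144 LBW infants and 180 infants with low weight on day 4 under equal randomization" and claims that this "will provide 80% or greater power per weight stratum for intervention group comparison to detect a difference of 0.20". The same sentence then describes the power as being "for the entire study cohort after accounting for up to 20% loss to follow-up". The Abstract keeps only the per-stratum version: "this sample size provides ≥80% power per weight stratum for intervention group comparison to detect a difference of 0.20".

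The next sentence of Sample size reports precision for the "mean difference between WAZ at day 30 and WAZ at birth with 0.17 and 0.15 standard errors by intervention group, respectively", again for the whole cohort. The article gives no SD for day-30 WAZ and no significance level.

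The Outcomes section makes 0.20 the hypothesized effect: formula "will increase infant WAZ at 30 days of infant age by 0.20 compared to infants randomly assigned to recommendations for EBF". The Statistical analyses section describes one test of that hypothesis: "we will use a permutation test, permuting the infant feeding intervention assignment within the infant weight stratum". It describes no separate test in each stratum.

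**The concern.** A standard error of 0.15 to 0.17 is nearly as large as the 0.20 effect, and 80% power at two-sided 5% needs an effect about 2.8 times its standard error. The power sentence and the precision sentence therefore look irreconcilable. The power sentence also names two different comparisons, each stratum and the whole cohort, while the analysis section describes only the pooled one.

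The 0.20 is the trial's own hypothesis, and the article says the result is meant to inform feeding policy. If the sponsor, the DSMB and readers believe that each stratum had at least 80% power, they will take a null result as evidence that formula does not raise WAZ. With the true power well below half, a null result would say little about an effect of that size.

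**Working it through.** **Inputs from the Sample size section.** LBW 144 (72 per arm), day-4 180 (90 per arm), total 324 (162 per arm), 1:1. After 20% loss: 72 × 0.8 = 57.6, 90 × 0.8 = 72 and 162 × 0.8 = 129.6 per arm. Effect 0.20. Standard errors 0.17 and 0.15.

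**Assumption.** Two-sided alpha 0.05, since none is stated. One-sided levels are tried below.

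**1. What 80% power requires.** The between-arm SE must be at most 0.20 / (1.960 + 0.842) = 0.20 / 2.802 = 0.071. Since SE = SD × √(2/n), the largest SD allowed is 0.20 / (2.802 × √(2/n)):

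| Comparison | n per arm after loss | Largest SD for 80% |
|---|---|---|
| LBW | 57.6 | 0.38 |
| Day-4 | 72 | 0.43 |
| Pooled | 129.6 | 0.58 |

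Without any loss the limits are 0.43, 0.48 and 0.64.

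**2. Where 0.17 and 0.15 come from.** They reproduce as between-arm SEs in the two weight strata with SD 1.0 and no loss: √(2/72) = 0.167 and √(2/90) = 0.149. SD 0.9 with 20% loss fits too: 0.9 × √(2/57.6) = 0.168 and 0.9 × √(2/72) = 0.150. Their ratio, 0.17/0.15 = 1.13, is close to √(180/144) = 1.12, which also points to the strata. Within-arm SEs per country and stratum (36 and 45 per arm) give the same values at SD 1.0: √(1/36) = 0.167 and √(1/45) = 0.149.

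**3. Power with the stated SEs used directly as between-arm SEs.** Power = Φ(0.20/SE − 1.960).
- SE 0.17: Φ(1.176 − 1.960) = 22%.
- SE 0.15: Φ(1.333 − 1.960) = 27%.
- Pooled SE = 1/√(1/0.17² + 1/0.15²) = 0.112: 43%.

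Differences detectable with 80% power: 2.802 × 0.17 = 0.48, 2.802 × 0.15 = 0.42 and, pooled, 0.32.

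**4. Power by SD, with 20% loss (noncentral t, two-sided 5%, effect 0.20).**

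| SD | LBW | Day-4 | Pooled | Detectable at 80% (LBW / day-4 / pooled) |
|---|---|---|---|---|
| 1.0 | 19% | 22% | 36% | 0.52 / 0.47 / 0.35 |
| 0.9 | 22% | 26% | 43% | 0.47 / 0.42 / 0.31 |
| 0.7 | 33% | 40% | 63% | 0.37 / 0.33 / 0.24 |
| 0.6 | 43% | 51% | 76% | 0.31 / 0.28 / 0.21 |
| 0.5 | 57% | 66% | 89% | 0.26 / 0.23 / 0.17 |

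Eighty percent power for 0.20 within a stratum would need about 393 evaluable infants per arm at SD 1.0, or 318 at SD 0.9, against 57.6 and 72 expected.

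**5. Other readings.**
- *One SE per intervention group in the whole cohort, as literally worded.* SE of the difference = √(0.17² + 0.15²) = 0.227, power 14%.
- *Within-arm SEs per stratum.* Implied SD 1.27 to 1.44, power about 11–18% per stratum.
- *One-sided 5%, with the SEs as in step 3.* 32% and 38% per stratum, 55% pooled.
- *One-sided 10%, likewise.* 46% and 52% per stratum, 69% pooled.

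None reaches 80%.

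**The case against.** The strongest objection is that the SEs describe change from birth, whereas the primary outcome is day-30 WAZ, whose SD is not given. That is true, but it does not rescue the per-stratum claim. The SD of day-30 WAZ cannot be smaller than the SD of change minus the SD of birth WAZ. With a change SD of 0.9 to 1.0, getting down to 0.38 (LBW) or 0.43 (day-4) would need a birth-WAZ SD of at least 0.52–0.62 or 0.47–0.57, together with a perfect negative correlation between birth WAZ and change.

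Birth weights are confined to 2000–2499 g and 2500–2885 g. If weights are spread evenly and one WAZ unit near birth is 350–500 g (both assumptions), the birth-WAZ SD is (499/√12)/500 to (499/√12)/350 = 0.29–0.41 for LBW. For day-4 it is (385/√12)/500 to (385/√12)/350 = 0.22–0.32. Both are too small.

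Second, the SE sentence is itself badly worded. Equal allocation gives equal arms, so two different values by intervention group make little sense, and reading them as stratum SEs is an inference from how well they fit. That stands. The literal wording gives lower power, however, so the inference favours the plan.

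Third, the 80% may have been meant for the whole cohort. The pooled figure does depend more on the SD: 80% needs 0.58 or less, and the article does not print a day-30 SD that rules this out. At the SD its own standard errors imply, pooled power is still only 36–43%, and the Abstract makes the per-stratum claim without mention of the cohort.

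Last, alpha is assumed here, and the full protocol may state both alpha and the SD. Their absence from an article is not the point. The point is that the printed figures contradict each other.

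**Conclusion.** The concern holds. At least 80% power in each weight stratum for a 0.20 difference cannot be reconciled with standard errors of 0.15 to 0.17, under any reading of those figures or any alpha tried. At two-sided 5%, 20% loss and the SD of 0.9 to 1.0 that the standard errors imply, power is about 19–22% (LBW), 22–26% (day-4) and 36–43% pooled. On those assumptions the trial is more likely than not to miss a true 0.20 effect even when pooled.

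The exact percentages depend on the SD of day-30 WAZ and on alpha. At one-sided 5%, pooled power rises to 55% with the stated SEs, and pooled power passes 80% only if the SD is 0.58 or less at two-sided 5%. The per-stratum claim would need an SD of 0.38 to 0.43, which nothing in the article supports. The claim is wrong as written and must be corrected.

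**What to change.** Keep 324 dyads. In the Sample size section:

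- State alpha, and the SD assumed for day-30 WAZ with its source.
- Name the pooled comparison, stratified by weight, as the one the trial is powered for, in line with the Statistical analyses section.
- Restate its detectable difference with the SD shown. For example: about 130 per arm after 20% loss gives 80% power at two-sided 5% for a difference of 0.35 at SD 1.0, or 0.24 at SD 0.7. The sponsor should insert its own SD.
- Say which quantity, groups and numbers the standard errors 0.17 and 0.15 refer to.
- Delete the per-stratum 80% claim here and in the Abstract, and label stratum-specific results as estimates with confidence intervals.

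The cost is a few sentences in two places and no extra participants. The stated power becomes less favourable, but a null result can then be read correctly.

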### Data collection and quality assurance

Study data will be collected using standardized electronic data instruments and entered directly into study databases during study visits by trained study staff. Paper case report forms (pCRFs) will be used when electronic data collection is not feasible, and paper forms will be used to document informed consent, participant location information, adverse events, and protocol noncompliances. Any data obtained on pCRFs will be electronically entered into the study database as soon as possible and at least weekly. Data collected electronically will be uploaded to the secure study database at least weekly in a de-identified manner to a secure, password-protected server and extracted for statistical analyses. Participant information with personal identifiers will be stored in paper-based form in a locked filing cabinet in a secure and locked private office or on a password-protected secure server. To ensure accuracy and completeness, study data will be routinely reviewed by study site staff trained in quality control and assurance as well as through both remote monitoring and study site visits by the co-investigators who will conduct data quality assurance reviews, audits, and evaluation of the study safety and progress. Standard GCP will be followed to ensure accurate, reliable, and consistent data collection.

### Data management

Study data management activities including data entry and validation, data coding and cleaning, database quality control, adverse event reporting and tracking systems, preparation and submission of safety and compliance reports, and preparation of final study database will be overseen at the respective study sites in collaboration with University of California, San Francisco (UCSF) data management staff using Research Electronic Data Capture (REDCap) software. The study site teams will be responsible for maintaining, and storing securely, complete, accurate and current study records throughout the study including signed informed consent. Data queries will be resolved weekly, and missing data accounted for in statistical analyses. All data management activities will be in compliance with International Council on Harmonization (ICH) GCP E6, locally applicable institutional review board, regulatory, sponsoring organization, and institutional requirements for the protection of study participants and confidentiality of personal and health information. After publication of the primary results, the data underlying the findings will be made available in a self-service, online public data repository.

### Outcomes

The primary study outcome is infant WAZ at 30 days of infant age. We hypothesize that feeding formula to infants will increase infant WAZ at 30 days of infant age by 0.20 compared to infants randomly assigned to recommendations for EBF without supplementation. Secondary, exploratory, and safety study outcomes include infant WLZ at 30 days of infant age; WAZ, WLZ, and LAZ through 6 months of age; breastfeeding duration; abundance of *B*. *infantis* in the intestinal microbiota at 30 days of age; adverse events; and serious adverse events. We hypothesize that feeding formula will increase infant WLZ at 30 days of infant age and infant WAZ, WLZ, and LAZ through 6 months of age by 0.20 compared to infants randomly assigned to recommendations for EBF without supplementation. While we hypothesize that infant breastfeeding duration will not differ between these feeding interventions, we hypothesize that the abundance of *B*. *infantis* in the intestinal microbiota will be higher among infants at 30 days of age who receive formula than among those who do not. To ensure infant safety, the effect of formula on mortality will be assessed after every 20 randomized infants have completed 30 days of follow-up, and the effect of formula on mortality and SAEs will be assessed once 25% and once 50% of randomized participants have completed 30 days of follow-up.

### Statistical analyses

Our primary analysis will be intention-to-treat which will inform the primary global health policy question of whether recommending formula improves infant growth. In order to account for our planned stratified randomization, we will use a permutation test, permuting the infant feeding intervention assignment within the infant weight stratum, to determine the effect of formula on the primary outcome of WAZ at 30 days of infant age as well as on the secondary and exploratory outcomes of WLZ at 30 days, WAZ, WLZ and LAZ through 6 months, intestinal microbiota at 30 days of age, breastfeeding duration, and receipt of non-breast milk dietary intake between birth and 6 months of age.

To determine *B*. *infantis* abundance, stool samples will be shipped to University of California, Davis for analysis and assessed by 16S rRNA gene sequencing. Samples found to have sequences from the *Bifidobacteriaceae* family will be further subjected to analysis of bifidobacterial species-specific terminal restriction fragment length polymorphisms (Bif-TRFLP) to identify specific species of *Bifidobacterium*. Statistical differences in *B*. *infantis* abundance between supplemented and unsupplemented infants, while accounting for strata, will be assessed by mixed linear modeling. In additional exploratory analyses, we will use cluster and eigenstructure analyses (e.g., principal component analysis) for descriptive analysis of 16S rRNA gene abundance data, followed by adonis permutation tests for significance of associations with continuous or factor variables or Mantel tests for associations between distance matrices. For example, feeding intervention group is an important factor variable; a significant association of the 16S rRNA gene profile with group membership would suggest an effect of formula on microbiota. Additional exploratory analyses will be undertaken with supervised machine-learning approaches, in order to identify new and unexpected features unique to the intestinal environment of formula recipients. For example, random forests will be used to identify important features separating the microbiotas of formula from EBF recipients.

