**Eligibility criteria**	
Inclusion criteria for screening	• Infant < 6 hours old • Infant birth weight estimated at 1500–3500 grams (g) • Mother ≥ 18 years old • Mother intends to breastfeed • Mother with negative HIV test • Mother lives in study catchment area and anticipates availability for all study visits
Exclusion criteria for screening	• Infant a twin or multiple • Infant with known major congenital anomaly, including orofacial cleft, neural tube defect or congenital heart defect • Infant with World Health Organization (WHO) newborn or respiratory danger sign present, including lethargy or unconsciousness, no spontaneous movement, not feeding well, convulsions, raised temperature > 37.5 degrees Celsius, hyopthermia < 35.5 degrees Celsius, jaundice, very fast breathing ≥ 60 breaths/minute, severe chest indrawing, head nodding, flaring, or grunting • Contraindication to breastfeeding at each site as determined by the site’s national or sub-national health authorities • Mother with psychiatric or psychosocial barrier to study participation • Infant enrolled in another study • Mother has had another infant enrolled in this study • Mother unable or unwilling to complete all aspects of the protocol
Inclusion criteria for enrollment	• Infant < 6 hours of age with screening weight 2000–2885 g • All screening inclusion criteria met
Exclusion criteria for enrollment	• Infant < 6 hours of age with screening weight < 2000 g or > 2885 g • Any screening exclusion criteria met
Inclusion criteria for randomization at day 0	• Enrolled infant < 6 hours of age with screening weight 2000–2499 g • All screening inclusion criteria met
Exclusion criteria for randomization at day 0	• Any screening exclusion criteria met
Inclusion criteria for randomization on calendar day 4	• Enrolled infant with weight < 2600 g • All screening inclusion criteria met

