**Study visits**	
Day 0	• Informed consent obtained • Mother-infant identification number assigned • Infant and maternal contact information, sociodemographic characteristics, current clinical status, and medical history obtained • Infant weight, length, mid-upper arm circumference (MUAC), head circumference measured • Infant physical examination performed • Infant stool sample collected • Maternal weight, height, and MUAC measured • Randomization completed if eligible for randomization
Day 4	• Infant weight, length, MUAC, head circumference measured • Infant hemoglobin measured • Infant and household dietary survey administered • Infant adverse events recorded • Maternal hemoglobin measured • Randomization completed if not already randomized and eligible for randomization
Day 14	• Infant weight, length, MUAC, head circumference measured • Infant dietary survey administered • Infant adverse events recorded
Day 30	• Infant weight, length, MUAC, head circumference measured • Infant stool sample collected • Infant and household dietary survey administered • Infant adverse events recorded • Maternal breast milk sample collected
Day 60	• Infant weight, length, MUAC, head circumference measured • Infant and household dietary survey administered • Infant adverse events recorded • Milk transfer assessed
Day 180 (study exit)	• Infant weight, length, MUAC, head circumference, skin folds measured • Infant stool sample collected • Infant and household dietary survey administered • Infant adverse events recorded • Maternal weight, height, and MUAC measured

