### Randomization and study procedures

Following enrollment, trained study staff will perform day 0 study procedures (Table 1) according to the most recently approved version of the protocol (current V.2.1, January 2021). Randomization to intervention group will be stratified by country and by weight at time of randomization (day 0 weight 2000–2249g; day 0 weight 2250–2499g; day 4 weight 2250–2424g; day 4 weight 2425–2599g), with 1:1 randomization within each stratum. If the enrolled infant weighs 2000–2499g on day 0, the dyad will be randomized on day 0. If the enrolled infant weighs 2500-2885g on day 0, the dyad will not be randomized on day 0; no intervention will be given on day 0 and the study team will follow the infant and weigh the infant again on day 4. If the enrolled but not yet randomized infant weighs <2600g on day 4, the dyad will be randomized on day 4; however, if the enrolled but not yet randomized infant weighs ≥2600g or has a weight loss ≥10% of birth weight on day 4, the dyad will exit the study. Random allocation will be accessed through a password-protected secure program (randomize.net) on a study device. While study staff and mothers will not be blinded to intervention assignment, the study staff will have no foreknowledge of intervention assignment. Participants will be enrolled with complete concealment of intervention so that both study staff and participants will learn of intervention allocation upon randomization.

Various mitigation measures will be put in place to reduce the possibility that the study’s conduct will impact the acceptability or distribution of formula within the postpartum ward or healthcare provider counselling and support for breastfeeding. First, all formula will be kept out of sight of patients and healthcare providers in a locked cabinet or locked room unless in active use by study staff or participants. Second, study activities will occur in a private room within in the hospital or in the participant’s home rather than on the postpartum ward. Third, prior to randomization, formula will be stored in an opaque container, so that only mothers who are randomly assigned to the study intervention will see it. Fourth, the study will not advertise for participants and will not distribute any materials to participants other than those required by the respective ethics committees.

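### The primary permutation test of day-30 WAZ uses weight at randomisation only as coarse strata, names no continuous baseline covariate and does not mention country

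*Protocol article*

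**What the plan says.** The Outcomes section fixes the endpoint: "The primary study outcome is infant WAZ at 30 days of infant age". For its analysis, the Statistical analyses section says that, to reflect the stratified design, "we will use a permutation test, permuting the infant feeding intervention assignment within the infant weight stratum", and that this is done "to determine the effect of formula on the primary outcome of WAZ at 30 days of infant age". It states no test statistic and names no continuous baseline covariate.

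The section Randomization and study procedures describes the design: "Randomization to intervention group will be stratified by country and by weight at time of randomization". The weight bands are "day 0 weight 2000–2249g; day 0 weight 2250–2499g; day 4 weight 2250–2424g; day 4 weight 2425–2599g), with 1:1 randomization within each stratum". Two countries by four bands make eight randomisation strata. The Sample size section, however, applies the term weight stratum to two broader groups: 144 low-birth-weight (LBW) infants and 180 infants with low weight on day 4.

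Baseline size is known for every randomised infant. Enrolment in Table 1 requires "Infant < 6 hours of age with screening weight 2000–2885 g". Heavier infants are weighed again: "If the enrolled but not yet randomized infant weighs <2600g on day 4, the dyad will be randomized on day 4". Table 1 also schedules, at day 0, "Infant weight, length, mid-upper arm circumference (MUAC), head circumference measured", and the same four measures at day 4.

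**The concern.** Three things are left on the table.

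- **Within-band information.** The bands are 175 g or 250 g wide and defined in grams, while the outcome is a z-score. Differences in size inside a band stay in the residual variance, and length is not used at all.
- **Country.** The stated reason for permuting within strata is to match the stratified randomisation, but that randomisation is also stratified by country. Permuting across countries generates reassignments that the design does not aim for, and leaves any between-country difference in the reference distribution.
- **Which weight strata.** The term could mean the four bands of the randomisation section or the two broad groups of the Sample size section. The value of adjustment differs a good deal between the two.

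At stake is precision on the primary outcome. A baseline-adjusted statistic would use data already scheduled, with no extra visits or measurements.

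**Working it through.** **Inputs from the article.** N = 324 (144 LBW, 180 day 4), 1:1, loss up to 20%, target difference 0.20, power of at least 80% per weight stratum. The article gives no SD of day-30 WAZ, no alpha and no baseline-outcome correlation. I assume a two-sided alpha of 0.05 and show ranges for the rest.

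**1. The stated power.** With n evaluable infants per arm, 80% power for 0.20 needs SD = 0.20 × √(n/2) / (1.960 + 0.842).

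- LBW, n = 57.6: SD at most 0.383
- Day 4, n = 72: SD at most 0.428
- Whole cohort, n = 129.6: SD at most 0.575

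The only variability figures are standard errors of 0.17 and 0.15 for change in WAZ from birth. If they are read as between-arm standard errors in the two groups after 20% loss, they give 0.17/√(2/57.6) = 0.91 and 0.15/√(2/72) = 0.90. Power would then be about 22%, 27% and 43%. This reading is an assumption, since the wording is ambiguous and the figures concern change. The stated 80% is not reproduced. I therefore use SD 0.575 and 0.9 as two illustrative cases.

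**2. What the bands already absorb.** Assume weights uniform within each range. The SD falls from 500/√12 = 144 g to 250/√12 = 72 g in LBW infants, and from 350/√12 = 101 g to 175/√12 = 51 g in day-4 infants. Either way, 1 − (1/2)² = 75% of the weight variance within the group is removed by the bands.

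**3. Gain by within-stratum correlation r.** The variance is multiplied by 1 − r². Evaluable infants: 324 × 0.8 = 259.

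- r = 0.2: variance down 4%; 259/0.96 = 270 equivalent infants
- r = 0.3: variance down 9%; 259/0.91 = 285
- r = 0.5: variance down 25%; 259/0.75 = 345

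**4. Which r is plausible from weight alone.** Let ρ be the correlation within the two broad groups. After the bands take 75% of the weight variance, r² = 0.25ρ²/(1 − 0.75ρ²).

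- ρ = 0.3 gives r² = 0.0225/0.9325 = 0.024 (r = 0.16)
- ρ = 0.5 gives r² = 0.0625/0.8125 = 0.077 (r = 0.28)
- To reach r = 0.5, ρ² must be 0.57, so ρ = 0.76

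The lower rows of step 3 are therefore the likelier ones for weight. What length would add cannot be computed from the article.

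**5. Power by simulation.** Settings: 4,000 runs, 116 + 144 infants, true difference 0.20, weights uniform within bands, balanced allocation in each band. Regression t-tests stand in for the permutation test, and country is not modelled.

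| SD | ρ | Two groups | Four bands | Four bands + continuous weight |
|---|---|---|---|---|
| 0.9 | 0.2 | 42.7% | 43.9% | 44.4% |
| 0.9 | 0.3 | 42.6% | 45.4% | 46.1% |
| 0.9 | 0.5 | 42.2% | 50.6% | 53.9% |
| 0.9 | 0.7 | 41.5% | 61.4% | 69.6% |
| 0.575 | 0.2 | 80.0% | 80.8% | 81.0% |
| 0.575 | 0.3 | 79.9% | 82.2% | 82.9% |
| 0.575 | 0.5 | 82.3% | 87.4% | 89.1% |
| 0.575 | 0.7 | 84.4% | 94.2% | 97.6% |

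Over the four bands, continuous weight adds about 0 to 3 points for ρ up to 0.5, and 3 to 8 points at ρ = 0.7. Over the two broad groups, at SD 0.9, the last column is higher by about 2, 4, 12 and 28 points.

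**6. Does it repair power?** At SD 0.9 with 20% loss, 80% power for the whole cohort needs about 795 infants unadjusted, 598 at ρ = 0.5 and 408 at ρ = 0.7, against 324 planned.

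**The case against.** The strongest reply is that permuting within weight strata is a valid analysis that respects the design, and that the four bands already take most of the weight information. That is right. A reader who looks only at the absence of a covariate might infer that the primary comparison ignores weight at randomisation. It does not, because the strata are defined by that weight.

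Second, a condensed article may leave the test statistic, covariates and interval method to an analysis plan that is not shown, and that plan may already use an adjusted statistic. This stands as a caution. But the article does state how baseline weight and the stratification are handled, and that description contains neither a continuous term nor country.

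A reader might also infer that the trial will report only a p-value. The article does not say so. It frames its hypothesis as a difference of 0.20 and plans to estimate mean changes in WAZ.

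Finally, it is tempting to say that adjustment would remove imbalance caused by loss. It would deal only with the covariates in the model. Unequal loss across bands does not by itself invalidate a test that conditions on the infants observed in each band.

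**Conclusion.** The point holds as one of efficiency and of matching the design, not of validity. The planned primary test uses weight at randomisation only in coarse categories, names no continuous baseline WAZ or length, and does not mention country.

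With the four bands as permutation strata, the likely gain is modest: a variance reduction of about 4% to 9% if the within-stratum correlation is 0.2 to 0.3, or about 0 to 3 power points from weight alone for ρ up to 0.5. If only the two broad groups are meant, the gain is larger, about 4 points at ρ = 0.3 and 12 at ρ = 0.5 with SD 0.9. All of these rest on assumed correlations, assumed SDs and uniform weights within bands. The effects of length and country are not quantified.

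A reader might infer that adjustment would rescue the trial's power. The figures do not support that. If the SD is near 0.9, the shortfall remains after adjustment and is a separate matter. The change is still worth making, because the data are already scheduled and there is no real downside.

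**What to change.** Specify the primary analysis as follows.

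- **Statistic:** the arm coefficient from a linear model of day-30 WAZ on arm, pre-randomisation WAZ (day 0 for infants randomised on day 0, day 4 for those randomised on day 4), pre-randomisation length, and indicators for the eight country-by-weight-band strata.
- **Reference distribution:** permute assignment within those same eight strata, which also settles what the weight stratum means.
- **Estimate:** report the coefficient with a 95% CI, from inverting the permutation test or from a robust standard error, as the primary estimate.
- **Sensitivity analysis:** the unadjusted mean difference.

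State that the baseline length used is taken before allocation is revealed, since staff are not blinded. The model has 1 + 2 + 8 = 11 coefficients for about 259 evaluable infants, so the cost in degrees of freedom is slight. The rest is wording in the analysis plan and a few lines of code, to be fixed before outcome data are compared by arm.
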